#### Insulin replacement therapy

Our intervention, continuous insulin replacement in the first week of life (NIRTURE study) aims to improve anabolism and insulin sensitivity, which may prevent the adaptations that lead to permanent changes in structure and metabolism.

As early growth is increasingly being shown to be important in terms of long-term metabolism [20-23] it is important to investigate their growth, body composition, insulin sensitivity and neuro-motor and neuro-endocrine development at least postnatally and in early childhood.

## **Aims of the study**

In the main multi-centre study 500 preterm infants will be randomised to receive either a continuous infusion of insulin for the first 7 days of life, or receive standard neonatal care. Aims of this amendment study are to investigate in a subpopulation of 60 preterms the effect of this early insulin replacement on growth and body composition, insulin sensitivity, the function of the HPA-axis and HPG-axis and neuro-motor development in infancy and during early childhood.

## **Hypothesis**

Relative insulin deficiency in the very low birth weight baby leads to profound catabolism, insulin resistance and hyperglycaemia during the first week of life. We hypothesize that insulin replacement may improve weight gain and IGF-I generation that could have implications for (brain) growth, body composition and later insulin sensitivity, neuro-endocrine and neuro-motor developmental outcomes by preventing the adaptations leading to permanent changes in organ structure and metabolism.

## **Questions:**

### Primary questions:

1. Does insulin replacement in preterm infants during the first week of life improve insulin sensitivity, early postnatal growth, catch up growth and body composition during the first years of life?
2. Does insulin replacement during the first week of life have implications for the development and function of the HPA and HPG axis?
3. Does insulin replacement during the first week of life have implications for the neuro-motor development during infancy and early childhood?

### Secondary questions:

1. Is insulin sensitivity related to early postnatal growth, catch up growth and body composition in early childhood?

## Methods

### Study population

Preterm infants that are included in the NIRTURE study will be included in this study indicating similar inclusion and exclusion criteria as in the NIRTURE study.

#### Inclusion criteria:

- birth weight < 1500g
- less than 24 hours of age
- requiring intensive care and in whom it is considered appropriate to continue intensive care
- written informed parental consent

#### Exclusion criteria

- maternal diabetes including gestational diabetes
- babies where the appropriateness of continuing intensive care is being discussed
- major congenital anomalies

### Design

Randomised controlled study

### Objectives

#### Primary:

1. Growth and catch up growth and body composition during the first two years corrected age

#### Secondary

1. Insulin sensitivity at the age of 6 months and 2 years
2. Adrenal function at the age of 6 months and 2 years
3. Development of the HPG axis postnatally until the age of 3 months
4. Neuro-motor and developmental outcome during the first 2 years corrected age

## **Measurements of outcomes**

Study design NIRTURE study (briefly)

In the multi-centre randomised controlled trial, VLBW infants (birth weight <1500g) will be randomised within 24 hours of delivery to either treatment with early fixed dose insulin (0,05 E/kg/hr) with 20% dextrose to maintain normoglycaemia, or to receive standard neonatal care.

Those randomised to treatment will receive a fixed dose of insulin combined with variable 20% dextrose support throughout the first week. Additional insulin will be infused if blood glucoses are consistently above 12 mmol/l, and an infusion of 20% dextrose will be started or increased if blood glucose falls to <4 mmol/l to prevent hypoglycaemia (blood glucose <2,6 mmol/l). Controls will receive standard neonatal care.

All babies will be monitored using a Minimed continuous glucose monitor for 7 days. Blood samples for measurement of IGF-1 (bioassay), IGFBP-1 and cytokines are taken on day 1, 3, 7 and 28 and a urine sample for measurement of 3-methylhistidine/creatinine ratio will be collected on day 7; all these samples are sent to Cambridge for analysis. Clinical data are recorded and after discharge all patients are followed in the outpatient clinic.

## **Measurement of outcomes amendment**

Growth and body composition

- Anthropometry according to Dauncey et al. [57] on day 7, at 32 weeks postmenstrual age, at expected date of delivery (40 weeks) and at the corrected age of three, six, twelve and twenty-four months.

Measurements include naked body weight (measured on a electronic scale to the nearest 5 g), crown-heel length (measured on a length board to nearest 1 mm) and head circumference (using a measuring tape to the nearest 1 mm). Crown-back length and bilateral lengths of the upper arms, lower arms and lower legs are measured (total length). In addition, chest circumference, bilateral circumferences of the upper arms, thighs and calves (total circumference) and bilateral skin-fold thickness at four sites (subscapular, abdominal, triceps and biceps) are measured.

- quantitative ultrasound of the second metacarpus [59] for assessment of bone mineral status on day 7, at 32 weeks postmenstrual age, at expected date of delivery (40 weeks) and at the corrected age of three, six, twelve and twenty-four months
- IGFBP-3 on day 7 and 28 and IGF-1, IGFBP-1 and IGFBP-3 in serum at the corrected age of 6 and 24 months

## 2. Insulin sensitivity

- fasting glucose and insulin in plasma and calculation of insulin sensitivity using the HOMA method [60] at the corrected age of 6 and 24 months

## 3. Adrenal function

- cortisol measurement in saliva at 24 months corrected age
- DHEAS will be measured in plasma and saliva at the corrected age of 6 and 24 months corrected age.

## 4. Blood pressure

- blood pressures: these are collected as part of the clinical data during hospital stay and will also be measured during follow-up in the outpatient clinic at 24 months corrected age

## 5. Gonadotrophins and steroids

- gonadotrophin (FSH and LH) measurements in urine on day 7 and 28, at 32 weeks postmenstrual age, at expected date of delivery (40 weeks) and at the corrected age of three months. As shown by Kuijper et al. urinary gonadotrophin levels are a proper reflection of the serum levels [61].
- oestrogens and androgens in urine on day 7 and 28, at 32 weeks postmenstrual age, at expected date of delivery (40 weeks) and at the corrected age of three months

## 6. Neurodevelopment during the first two 2 years of life according to routine follow up of preterms in the VUmc

- developmental tests: standardised neurological assessment according to Prechtl at expected date of delivery (0 months) and according to Touwen at the corrected age of 3, 6, 12 and 24 months [62,63,64]. Alberta Infant Motor Scale (AIMS) [65] and the motor Bayley Scales at a corrected age of 6 and 12 months. Psychomotor development indices

and mental development indices at 12 and 24 months corrected age. Current method used is the Bayley Scales of Infant Development II (BSID-II) Motor Scale [66]

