| Study Design              | Randomised controlled study.                                                                                                                                                                                         |
| Study Population          | Infants with birth weight <1500g and recruited within 24 hours of birth                                                                                                                                              |
| Number of Patients        | 60                                                                                                                                                                                                                   |
| Multicentre               | No                                                                                                                                                                                                                   |
| Allocation of Treatment   | Randomisation to treatment or control if all inclusion/exclusion criteria are met                                                                                                                                    |
| Primary Efficacy variable | Improved growth, body composition, neuro-motor development and function of the neuro-endocrine axes                                                                                                                  |

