## **Ethical considerations**

Taken the blood samples of the first project into account only at the corrected age of 6 and 24 months extra blood samples (total amount 1 ml) will be taken. These samples have to be taken prior to feeding. The sample size at the age of 7 days and 28 days for the first project will be increased with 250 µl; these blood samples are taken from the arterial line. Insertion of a central venous and arterial line in these very low birth weight infants is part of routine care. Taken the urine sample of the first project into account, 4 extra urine samples (5 ml) will be taken on day 28, at 32 weeks postmenstrual age and at the corrected age of 0 and 3 months. The sample size at the postnatal age of 7 days will be

increased with 5 ml. All urine samples are collected in a pediatric urine collection pouch.

It is important to notice that in this project most determinations in blood and urine are accomplished in samples that are already collected for clinical reasons; the remaining material is stored and used for analysis within this project.

Anthropometry and quantitative ultrasound will be performed on day 7, at 32 weeks postmenstrual age and at the corrected age of 0, 3, 6, 12 and 24 months. During hospitalisation this will be combined with routine nursing care to minimize the burden.

Saliva samples will be collected at the corrected age of 6 and 24 months.

Data of each subject will be stored in a case record form (CRF) and into a computer file for analysis. Patient data, blood, urine and saliva samples will be anonymised. After analysis, the data will be used for scientific presentations and publications in scientific journals. All data will be reported anonymously.

Unexpected findings will be reported to the pediatrician and the general practitioner in writing. The subjects will be insured according to the research insurance policy of the VU University medical center (see appendices).

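### The comparison is open in effect, and the protocol does not provide that those who measure the examiner-dependent outcomes are unaware of allocation

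*Protocol*

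**What the plan says.** **Treatment contrast.** The Protocol's Design section says only "Randomised controlled study". Under Measurements of outcomes, treated infants receive continuous fixed-dose insulin with variable 20% dextrose through the first week, and "Controls will receive standard neonatal care". No placebo or sham infusion is described.

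**Growth and body composition.** The primary objective is "Growth and catch up growth and body composition during the first two years corrected age". The amendment's measurement section specifies weight on an electronic scale, length by length board and head circumference by tape. It adds segment lengths, further circumferences, and "bilateral skin-fold thickness at four sites (subscapular, abdominal, triceps and biceps) are measured". There are seven anthropometry time points: day 7, 32 weeks postmenstrual age, term, and 3, 6, 12 and 24 months corrected age. Of the in-hospital anthropometry and ultrasound, Ethical considerations says: "During hospitalisation this will be combined with routine nursing care to minimize the burden".

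**Neuro-motor outcome.** Item 6 of the measurements is headed "Neurodevelopment during the first two 2 years of life according to routine follow up of preterms in the VUmc". It lists the Prechtl examination at term, Touwen at 3, 6, 12 and 24 months, the Alberta Infant Motor Scale (AIMS), and the Bayley scales. Its rank differs by section. The Secondary objectives list "Neuro-motor and developmental outcome during the first 2 years corrected age". The local summary, however, gives the primary efficacy variable as "Improved growth, body composition, neuro-motor development and function of the neuro-endocrine axes", and the third primary question is also about neuro-motor development.

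**Masking.** No section says whether the person who measures or examines knows the arm.

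**The concern.** A reading taken by hand or scored by judgement can move with what the examiner expects. The local summary words its efficacy variable as an improvement, so an expectation exists. If examiners know the arm, a small consistent shift can enter length, circumference, skinfold or motor-score readings. Such a shift is not reduced by a larger sample, and the analysis cannot separate it from a treatment effect.

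The matter cannot be left to a statistical analysis plan. Who measures, and what they know, has to be settled before the first visit. These measurements belong to this amendment, which specifies instruments, precision and timing in detail, so this is the natural place for the rule.

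**Working it through.** **1. Which outcomes are exposed**

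| Outcome | How obtained | Depends on examiner? | Rank in the Protocol |
|---|---|---|---|
| Weight | electronic scale, nearest 5 g | little | part of primary objective |
| Length, circumferences, skinfolds | length board, tape, manual skinfolds | yes | part of primary objective |
| Prechtl, Touwen, AIMS, Bayley | examiner-scored, standardised tests | yes | secondary in Objectives; primary in the local summary and Questions |
| IGF-1, binding proteins, insulin, glucose, DHEAS, cortisol, gonadotrophins, urinary steroids | laboratory assay | little | secondary objectives or supporting measures |

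**2. When masking is possible.** The infusion covers the first week of life. Day 7 falls in or at the end of that week, and the 32-week reading comes early in the infant's course. The other five of the seven anthropometry visits, and every neuro-motor visit, are at term age or later.

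**3. The plan's own figure.** Sample size consideration states 30 evaluable infants per group, a difference of 0.5 SDS, 80% power and α = 0.05. It gives neither the SD nor the sidedness. I take the test as two-sided.

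- With SD = 1.0 SDS (assumed): n per group = 2 × (1.960 + 0.842)² × 1.0² / 0.5² ≈ 62.8, so 63. With 30 per group the power is about 48% by the noncentral t.
- The SD that would reproduce 30 per group: 0.5 × √(30/2) / (1.960 + 0.842) ≈ 0.69 SDS.

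The stated figure is therefore reproduced only at an SD of about 0.69 SDS, which the Protocol does not give. That is a separate matter. It is used here only to set a range of SDs for step 5.

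**4. Effect of an assessor shift, in SD units.** Inputs: n = 30 per arm (Sample size consideration); unpaired t-test at p < 0.05 (Statistical analysis), taken as two-sided; no true effect. The shift d is my assumption, because the Protocol gives no figure for reader bias.

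Noncentrality λ = d × √(n/2) = d × √15 = 3.873 d; degrees of freedom 58; critical value 2.002. Rejection probability = P(T > 2.002) + P(T < −2.002), with T noncentral t.

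| Shift d (SD) | λ | False-positive rate per test |
|---|---|---|
| 0 | 0 | 5.0% |
| 0.20 | 0.775 | 11.9% |
| 0.25 | 0.968 | 15.9% |
| 0.30 | 1.162 | 20.8% |

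**5. The same shift in SDS units.** Converting to SDS needs the unstated SD. At 1.0 SDS the table stands unchanged. At 0.69 SDS, d equals the shift divided by 0.69:

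- 0.20 SDS gives d = 0.29 and a rate of about 20%.
- 0.25 SDS gives d = 0.36 and a rate of about 28%.
- 0.30 SDS gives d = 0.43 and a rate of about 38%.

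These rates apply to each affected measure at each visit, since the plan tests every time point separately.

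**The case against.** **Silence is not exclusion.** The Protocol contains no statement that the trial is open label or that assessors are unmasked, and it describes the parent study only briefly. This stands. Open treatment is a fair inference from an infusion compared with standard care without a described placebo. Unmasked assessment is not stated, and the supportable claim is only that masking is not provided for.

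**Stronger readings a reader might infer.**
- *All these endpoints are taken in routine care.* The text says so only for in-hospital anthropometry and ultrasound and for neurodevelopment, not for outpatient anthropometry.
- *The follow-up examiner holds the neonatal record, or the day-7 measurer is the bedside nurse.* No section says who measures or what records are to hand.
- *The main endpoints as a whole are compromised.* Weight and the assays are little affected, the neurological assessment is described as standardised, and the Objectives rank neuro-motor outcome as secondary.
- *Skinfolds will drift towards the hypothesis.* The Protocol does not say whether a thicker or thinner fold would count as improved body composition, so the direction is unclear. A consistent direction is more plausible for length, head circumference and motor scores.
- *A 0.25 SD shift is half the target difference.* That is true only if the SD is 1.0 SDS. At 0.69 SDS it is 0.25 × 0.69 ≈ 0.17 SDS, about a third of 0.5.

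**Masking may leak.** With one centre and 60 infants, some follow-up staff may have cared for the infant in the first week, and parents may mention the arm. This stands too. It is a reason to record unmasking, not to omit the attempt.

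**Conclusion.** The concern holds in limited form. Treatment is open in effect to ward staff, and the protocol does not provide that assessors of length, circumferences, skinfolds, Prechtl, Touwen, AIMS and Bayley are unaware of allocation. The anthropometric part of the primary objective carries the point even if neuro-motor outcome is taken as secondary.

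The size is illustrative: about 12%, 16% or 21% false positives per test for assumed shifts of 0.2, 0.25 or 0.3 SD, against a nominal 5%. It rests on 30 evaluable infants per arm, a two-sided test and no true effect. The documents do not show that such a shift would occur, or how large it would be. They show only that nothing in the plan guards against it. I rate this a cheap improvement.

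**What to change.** Add one paragraph to the growth and body composition section and to item 6 (Neurodevelopment):

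- From the term-age visit onward, anthropometry, ultrasound and all neuro-motor tests are done by existing follow-up staff who have not been told the allocation and, where possible, did not care for the infant in the infusion week.
- The arm is kept off the study visit form, and parents are asked not to mention it.
- At each visit the examiner records on the case record form whether the arm became known.
- The day-7 and 32-week readings are labelled as unmasked, and the body-composition conclusion does not rest on them alone.

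Leave the clinical discharge summary as it is. The change concerns study forms only.

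The cost is the paragraph, one tick-box, and some care over which of the existing staff see which infant. No extra assessor is needed, and sample size, treatment and visit schedule are unchanged. The downside is some accidental unmasking at a single centre, which the tick-box makes visible.

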## **Assays**

### Blood sample analysis:

Blood samples collected will be stored at -80°C until IGF-1/IGFBP-1/IGFBP-3/insulin/ DHEAS are determined by immunoassay (see page 32).

Glucose will be measured by the hexokinase method.

### Saliva sample analysis:

Saliva samples collected will be stored at -20°C until DHEAS and Cortisol are determined by immunoassay (see page 32).

### Urine sample analysis

Urine samples are collected in a pediatric urine collection pouch and will be stored at -20°C until FSH and LH are determined.

Gonadotrophin levels will be measured by the Architect method using reagents obtained from Abbott Laboratories (Diagnostics Division Abbott Park, Illinois, USA) (see page 32).

Oestrogens (ER $\alpha$  CALUX) and androgens (AR CALUX) levels in urine will be measured using the Chemically Activated LUCiferase eXpression (CALUX) reporter gene assays [67,68].

## **Sample size consideration**

Bolt et al [56] studied growth and body composition in 15 SGA and 26 AGA preterm born infants during the first 2 years of life. They found that growth expressed as anthropometry according to Dauncey [57], IGF-1 and IGFBP-3 were significantly lower in SGA than in AGA infants ( $p < 0.01$ ). Catch up growth during the first year of life was significantly higher in SGA infants compared to AGA infants ( $p < 0.01$ ).

In addition, growth and body composition was studied in 14 preterm infants with chronic lung disease and treated with corticosteroids to facilitate weaning from

the ventilator and 18 preterm controls during the first 2 years of life [58]. Body composition at term and 3 months corrected age in preterm infants treated with dexamethasone for chronic lung disease, who received extra caloric intake until term age, did not differ from preterm infants without CLD.

Based on the results of both studies in combination with power calculation it is expected that groups of 30 fully evaluable subjects (insulin treated vs. controls) will be sufficient to detect a difference of 0.5 SDS in growth parameters with a power of 80% at  $\alpha=0.05$ .

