## Abbreviations

|       |                                            |
|-------|--------------------------------------------|
| ACTH  | adrenocorticotrophic hormone               |
| AGA   | appropriate for gestational age            |
| CRH   | corticotrophin releasing hormone           |
| DEXA  | dual energy x-ray absorptiometry           |
| FSH   | follicle stimulating hormone               |
| GA    | gestational age                            |
| GH    | growth hormone                             |
| GH-BP | GH-binding protein                         |
| HPA   | hypothalamic-pituitary-adrenal             |
| HPG   | hypothalamic-pituitary-gonadal             |
| IGF   | insulin-like growth factor                 |
| IGFBP | insulin-like growth factor-binding protein |
| IUGR  | intrauterine growth retardation            |
| LBW   | low birth weight                           |
| LH    | luteinizing hormone                        |
| SGA   | small for gestational age                  |
| SDS   | standard deviation score                   |
| VLBW  | very low birth weight                      |

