### **Statistical analysis**

Results are presented as mean  $\pm$  standard deviation. We will compare the results of infants treated with insulin to those receiving standard care on an intention to treat basis and within each group we will also compare the results of SGA infants to AGA infants.

Comparison between the groups on all different time points will be analysed using the unpaired t-test.

Within group differences between different time points and differences between the groups in the changes of the values in time will be analysed with repeated measures analysis of variance (ANOVA).

A p value of  $<0.05$  will be considered as statistically significant

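### The stated 80% power to detect 0.5 SDS with 30 infants per group does not reproduce for the planned unpaired t-test: at an assumed SD of 1.0 SDS it is about 48%, and the protocol states no SD

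*Protocol*

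**What the plan says.** The Sample size consideration section summarises two earlier cohorts of preterm infants. From these, together with an unspecified power calculation, it arrives at a planned size of "groups of 30 fully evaluable subjects (insulin treated vs. controls"). At alpha 0.05 the protocol regards this number as "sufficient to detect a difference of 0.5 SDS in growth parameters with a power of 80" per cent. The total of 60 appears in Summary of the local amendment and in Aims of the study ("in a subpopulation of 60 preterms the effect of this early insulin replacement on growth and body composition"). Growth, catch-up growth and body composition form the primary objective.

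The Statistical analysis section names two between-group analyses. The first reads "Comparison between the groups on all different time points will be analysed using the unpaired t-test". The second reads "differences between the groups in the changes of the values in time will be analysed with repeated measures analysis of variance (ANOVA"). The sample size section does not say which of them the 80% refers to. It states no SD, no correlation between visits and no sidedness. The list of abbreviations expands SDS as "standard deviation score".

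**The concern.** A difference in SDS is already expressed in units of the reference population's standard deviation. Read at face value, 0.5 SDS is a standardised effect of 0.5, and a two-group t-test for an effect of that size usually needs about twice the 30 per group given here.

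This sentence is the only quantitative justification for the sample size, and it concerns the primary objective. If the power for 0.5 SDS is well below 80%, the protocol promises a sensitivity that the design may not have. A non-significant growth result would then say less about an effect of 0.5 SDS than the sentence suggests.

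**Working it through.** **Inputs from the protocol.** n = 30 per group, difference 0.5 SDS, alpha 0.05, stated power 80% (Sample size consideration); unpaired t-test (Statistical analysis). The planned total of 60 equals 2 × 30, so 30 evaluable per group is the most that 60 infants can give.

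**Input not in the protocol.** The between-infant SD of the score. I assume 1.0 SDS, the reference unit, and vary it below. Sidedness is also not stated; two-sided is taken first.

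**Attempt to reproduce the 80%.** The t-test has 2 × 30 − 2 = 58 degrees of freedom. The noncentrality parameter is difference / (SD × √(2/n)) = 0.5 / (1.0 × √(2/30)) = 0.5 / 0.2582 = 1.94. The two-sided critical value is 2.00. The noncentral t distribution gives power of 47.8%, and the normal approximation gives 49.1%. The stated 80% is not reproduced.

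**Other standard readings at SD 1.0.**
- One-sided alpha 0.05: 60.6%.
- One-sample or paired formula with n = 30: 75%.
- 60 taken as the number per group: 77.5%.

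None of these gives 80%.

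**Solving for the other quantities (two-sided, SD 1.0).**
- Difference detectable with 80% power at 30 per group: 0.736 SDS (normal approximation 0.723).
- Number per group for 80% power at 0.5 SDS: 64 (63 by the normal approximation).
- SD at which 30 per group gives 80% power for 0.5 SDS: 0.5 / 0.736 = 0.68. One-sided, it is 0.77.

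**Sensitivity to the assumed SD (two-sided t-test, n = 30 per group, difference 0.5 SDS).**

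| SD (SDS) | Power | Detectable at 80% (0.736 × SD) |
|---|---|---|
| 0.6 | 89% | 0.44 |
| 0.68 | 80% | 0.50 |
| 0.8 | 66% | 0.59 |
| 0.9 | 56% | 0.66 |
| 1.0 | 48% | 0.74 |
| 1.2 | 35% | 0.88 |

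An SD of 0.68 means a variance of 0.68² = 0.46, under half the reference variance.

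**The repeated measures analysis (SD 1.0 at each visit, common correlation r).** Power of 80% needs an effective variance of about 0.462.
- Change between two visits: variance 2(1 − r). Setting 2(1 − r) = 0.462 gives r = 0.77. At r = 0.5 power is 48%; at r = 0.8 it is 85%.
- Mean of the seven anthropometry visits: variance (1 + 6r)/7. Setting this to 0.462 gives r = 0.37, so the correlation must be that low or lower. At r = 0.3 power is 85%; at r = 0.5 it is 71%.

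The two routes need opposite conditions, a high correlation for the first and a low one for the second. The protocol states neither.

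**Precision.** At SD 1.0 the half-width of the 95% confidence interval for the group difference is about 2.00 × 0.2582 = 0.52 SDS.

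**The case against.** The strongest reply is that the protocol gives no SD. A standard deviation score has SD 1 in its reference population, but the spread among the trial's infants is a separate quantity. The protocol says that the calculation drew on two cohorts, and a smaller SD may have come from them. A reader might infer that those cohorts supply no SD. The document does not support that: only short summaries are visible, and all that can be said is that the protocol quotes no SD from them. It does give some reason to doubt a narrow spread, because each arm will contain both SGA and AGA infants, and the protocol reports that growth differed between those groups (p < 0.01) in the first cohort.

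A second reply is that the t-test is not the only planned comparison. Repeated measures ANOVA is planned for changes over time, and catch-up growth is part of the primary objective. This stands as a limit on certainty. It does not restore the 80%, because the sample size section neither ties its figure to that analysis nor states a correlation.

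A third reply concerns consequences. A reader might infer that a true 0.5 SDS effect would be missed more often than found. That holds only above an SD of about 0.97; at 0.9 power is 56%, and at 0.8 it is 66%. Nor does the protocol say that a null result will be taken to exclude 0.5 SDS.

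**Conclusion.** The concern holds in conditional form. The 80% cannot be reproduced from what the protocol states. On the natural reading of the SDS scale (SD 1.0, two-sided unpaired t-test) it is too high by about 32 percentage points: 48% against 80%. The design detects about 0.74 SDS with 80% power, and 0.5 SDS would need 64 per group rather than 30. One-sided testing raises power only to 61%.

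It would go too far to say that power is 48% under every input. The stated figure would be right at an SD of about 0.68 or less, or for the repeated measures analysis under a suitable correlation, but the protocol gives no such value. The required 64 per group lies close to the planned total of 60, so a reader might suspect that total and per-group numbers were confused. Nothing in the document shows this.

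**What to change.** In Sample size consideration, replace the power sentence with wording such as: *30 evaluable infants per group give 80% power (unpaired t-test, two-sided alpha 0.05, assumed SD 1.0 SDS) to detect 0.74 SDS; power for 0.5 SDS is about 48%.* Add the range by SD: 89% at 0.6, 80% at 0.68, 66% at 0.8, 56% at 0.9 and 35% at 1.2.

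If the sponsor holds data supporting an SD of 0.68 or less, or based the figure on the repeated measures analysis with a known correlation, state that input and its source instead, and name the analysis to which the 80% applies.

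In either case, add that a non-significant result does not by itself exclude 0.5 SDS and will be interpreted from the confidence interval.

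The cost is a change of protocol wording and a less favourable stated figure. No extra patients and no move to ANCOVA are required. Restating the power does, however, invite the question of whether 60 infants suffice for the primary objective, and the sponsor should be ready to answer it.
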